## Methods

This manuscript includes information on all Standard Protocol Items: Recommendations for Interventional Trials (SPIRIT, checklist in Additional file 1) [47].

### Participants and recruitment

Recruitment of participants takes place at the Department of Child and Adolescent Psychiatry, Psychosomatics and Psychotherapy at the University Hospital of Psychiatry and Psychotherapy Tuebingen, Germany, and is embedded in the regular routines of the hospital (see Fig. 1). Potentially, all children and adolescents who are patients in the department’s child therapy ward, adolescent therapy ward, day hospital for children, or day hospital for adolescents; a relevant primary attachment figure (a parent or caregiver from a residential group); and optionally teachers from the child’s or adolescent’s school are eligible to participate in the study. The children and adolescents are usually between 6 and 18 years old. We aim to investigate *N* = 50 triplets (*n* = 25 children/adolescents, *n* = 25 parents, and *n* = 25 teachers in each group). While sufficient German language skills are an inclusion criterion, the specific indication for partial or full inpatient treatment, type of diagnosis, or time of discharge are not. Transition to regular outpatient treatment is also not an exclusion criterion, as DigiPuR aims to form a good transition to outpatient structures in coordination with all involved parties. The study exclusion criteria are kept minimal to allow as many patients as possible to access the aftercare program. DigiPuR study staff are in weekly communication with the therapists in the department’s therapy wards and day hospitals to identify participants. In case of acute psychological strains during the study, the procedure is analogous to conventional psychotherapy with emergency presentation at the responsible hospital. If emergency care result in an inpatient stay of less than 2 weeks, participation in the study is continued (ambulatory assessment continues, intervention components resume after discharge) and, in case of more than 2 weeks, discontinued. A pilot phase of the study was conducted in early 2021, followed by recruitment from March 2021 to June 2022.

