
### Hypotheses

DigiPuR examines whether the reintegration of children and adolescents after their stay in a psychiatric hospital can be facilitated by digitally supported, cross-contextual aftercare. Four hypotheses emerge for the primary outcomes. First, we hypothesize readmission rates to be lower at the post- and follow-up time points in the intervention group than in the control group (treatment-as-usual; TAU). Second, we hypothesize satisfaction with treatment to be higher at the post-time point in the intervention group than in the control group. Third, we hypothesize health-related quality of life to develop better over time (pre-post follow-up) in the intervention group than in the control group. We do not necessarily expect the intervention group to improve in absolute values over time, as measures can decline after discharge, indicated by high rates of readmissions [8, 10]. Rather, we expect the intervention group to develop better over time than the control group, meaning that even a stabilization of values might be considered a success. Fourth, we hypothesize symptom severity to develop better over time (pre-post follow-up) in the intervention group than in the control group. In line with the last two hypotheses, a better development in the intervention group than in the control group is also expected for the secondary outcomes on stress, self-efficacy, and perceived competence, including ambulatory assessment on well-being, affect, sleep quality, school situation, and social relationships.

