#### Instruments

The instruments used in DigiPuR (see Table 1) are chosen to cover the five domains (symptoms, functioning, consumer perspectives, environments, systems) of the comprehensive conceptual model of outcomes of mental health care for children and adolescents [46]. The instruments and scales used in the pre-post-follow-up assessment and the ambulatory assessment are briefly described in the following, sorted according to the five domains. Item formulations were adapted where necessary so that they are understandable and suitable for both children and adolescents. Items are only presented if their content is relevant to the respective group (e.g. items on satisfaction with the program for video calls only when it was used). Primary outcomes are number of readmissions, satisfaction with treatment, health-related quality of life, and symptom severity; all others are secondary outcomes (see Table 1). As there is a great heterogeneity of diagnoses in the patient sample, the evaluation aims to assess the reintegration phase and the well-being of patients globally and across disorders. General constructs relevant to different disorders were selected and instruments were used for comparability across the age range.

**Table 1 Tab1:** Overview of assessed outcomes, assigned domains, instruments, and raters at the different study time points

Outcome	Domain [46]	Instrument or scale	Rater	Study period				
				Enrollment	Allocation	Post-allocation		
				Admission	Ambulatory assessment (2 weeks before discharge until 8 weeks after)	Pre (discharge)	Post (8 weeks after discharge)	Follow-up (24 and 36 weeks after discharge)
Symptom severity	Symptoms	DISYPS-III SCREEN [52]	CA, P*, T*	x		x	x	x
Stress vulnerability and coping strategies	Symptoms (part 1), functioning (part 2)	Adapted from SSKJ-3-8R (parts 1 and 2) [53]	CA	x		x	x	x
Self-efficacy	Functioning	WIRKSCHUL [54], WIRKSOZ [54], WIRKLEHR [54], WIRKELTERN (self-development)	CA, P, T	x		x	x	x
Health-related quality of life	Consumer perspectives, environment	KIDSCREEN-27 [55]	CA, P*	x		x	x	x
Occupational well-being	Environment	Emotional exhaustion [56], enthusiasm for teaching [56]	T			x	x	x
Satisfaction with treatment	Consumer perspectives	Adapted from FBB [57]	CA, P, T, TH				x	
Satisfaction with technical components	Consumer perspectives	SUS [58], self-development	CA, P, T, TH				x	
Expectation of change	Consumer perspectives	Adapted from patient’s expectation of change [59]	CA, P			x		

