#### Statistical analyses

All analyses are conducted using R software [48]. All outcome variables measured pre-post-follow-up will be analyzed with separate mixed ANOVAs. Preprocessing of the data and calculation of individual values will be done according to the respective manual. Predictors will be group (intervention vs. control) and time point, as well as their interaction. Treatment success would be demonstrated by a significant interaction effect of group and time point, being shown, through adequate post hoc test, to be due to different time-effects in the two groups. We do not necessarily expect the intervention group to improve in absolute values over time, as measures can decline after discharge. Rather, we expect the intervention group to develop better over time than the control group, meaning that even a stabilization of values might be considered a success. This better development in the intervention group than in the control group should be evident in the information provided by patients themselves, as well as by parents and teachers.

The successful reintegration into daily (school) life is conceptualized besides the pre-post-follow-up assessment by the data collected in the ambulatory assessment. All ambulatory assessment data will be analyzed with multi-level models [78]. We expect the reports from patients, parents, and teachers in the intervention group to show a significantly more positive trend over time in terms of their general well-being, affect, sleep quality, school absenteeism, situation in class, and the relationship with parents, peers, and teachers, than those in the control group. Statistically, these effects are shown by a significant interaction of the within-person time trends of these reports with group membership, being due to participants in the intervention group developing better (or less bad) than participants in the control group. Variables will be adequately centered, and appropriate fixed and random effects will be included in the models.

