Few missing data are expected due to ongoing monitoring. Missing data from single items of the standardized questionnaires will be handled appropriately according to the instructions in the manual. In case of complete questionnaires missing for a participant, this participant will be excluded from all ANOVAs containing this questionnaire. As multi-level models can handle missing data quite well, if they are at least missing at random, no data will be excluded from those analyses. However, appropriate variables (e.g., age, symptom severity) will be used to investigate if the missingness structure can be explained by them, rendering it to be not at random. In that case, those variables will be included in the according models to account for this non-randomness.

Due to the confidentiality of patient health data, data sets cannot be made publicly available. Access is only granted to study management who supervise data management and have a duty of confidentiality.

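### A long emergency inpatient stay ends study participation, and the ANOVA missing-data rule then deletes the patient, so an event tied to one primary outcome decides who is analysed for two others

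*Protocol article*

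**What the plan says.** Four parts of the protocol article bear on this.

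- **Participants and recruitment.** The rule opens with "If emergency care result in an inpatient stay of less than 2 weeks" and goes on: "participation in the study is continued (ambulatory assessment continues, intervention components resume after discharge) and, in case of more than 2 weeks, discontinued".
- **Instruments.** "Primary outcomes are number of readmissions, satisfaction with treatment, health-related quality of life, and symptom severity".
- **Hypotheses.** For the first of these outcomes, "we hypothesize readmission rates to be lower at the post- and follow-up time points in the intervention group than in the control group".
- **Statistical analyses.** "All outcome variables measured pre-post-follow-up will be analyzed with separate mixed ANOVAs", with success defined as a group-by-time interaction. On missing data: "In case of complete questionnaires missing for a participant, this participant will be excluded from all ANOVAs containing this questionnaire". A more generous rule, "no data will be excluded from those analyses", applies only to the multi-level models for the daily ambulatory data.

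The same section expects few missing data because returns are monitored. The Background gives reported rehospitalisation rates of 12 to 57%, with most readmissions in the first 3 months after discharge. The article gives no frequency for emergency stays of more than 2 weeks.

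**The concern.** An emergency inpatient stay of more than 2 weeks after discharge is in substance a readmission. The rule makes it a reason to leave the study, not only a reason to stop aftercare. Two consequences follow on the literal reading.

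First, the patients whose course after discharge was worst supply no later quality-of-life or symptom scores. Second, because the ANOVAs drop anyone with a whole questionnaire missing, their admission and discharge scores go too. Monitoring of returns cannot prevent this, since the gap is created by rule.

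What is at stake is the randomised comparison for two of the four primary outcomes. Membership of the analysed set would depend on something that happens after randomisation and that the trial itself expects to differ between arms. The Hypotheses section counts mere stabilisation as success because scores can fall after discharge. The rule takes out the patients in whom such a fall is most likely.

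**Working it through.** **Step 1: the chain of rules.**

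1. A stay of more than 2 weeks ends study participation (Participants and recruitment).
2. The quality-of-life and symptom questionnaires are due at 8, 24 and 36 weeks (Pre-post-follow-up assessment). As most readmissions fall within 3 months, they usually precede the 24- and 36-week surveys, and some precede the 8-week survey.
3. A missing complete questionnaire removes the patient from the ANOVA for that instrument at all time points (Statistical analyses).
4. The triggering event is hypothesised to be rarer under the intervention (Hypotheses).

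Each link is stated text except one: that ending participation includes the later surveys. That is the literal meaning of the sentence, but it is not spelled out.

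**Step 2: scale.** The plan gives no figure to reproduce on this point. Its only relevant number is 25 patients per group, so each exclusion costs 1/25 = 4% of an arm. The following is illustrative.

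Inputs:
- Control readmission rate: 12% and 57% (the Background's limits) and 30% (an assumed middle value).
- Share of readmissions that are emergency stays of more than 2 weeks: 50% or 100% (assumed).
- Risk ratio, intervention to control: 0.5 or 1.0 (assumed).
- Correlation ρ between the risk of removal and the analysed outcome: 0.3 or 0.6 (assumed).

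If a proportion p of an arm is removed, the mean of those left improves by ρ·φ(z)/(1−p) SD, where z is the (1−p) quantile of the standard normal and φ its density. The shift in the group difference is the intervention-arm value minus the control-arm value.

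Worked example: control p = 0.30, intervention p = 0.15, ρ = 0.6.
- Control: 0.6 × 0.348/0.70 = 0.298.
- Intervention: 0.6 × 0.233/0.85 = 0.165.
- Shift: 0.165 − 0.298 = −0.133 SD.

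All cases with risk ratio 0.5:

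| Control readmission | Share qualifying | Removed of 25, control / intervention | Shift, ρ = 0.3 | Shift, ρ = 0.6 |
|---|---|---|---|---|
| 12% | half | 1.5 / 0.8 | −0.017 | −0.034 |
| 12% | all | 3.0 / 1.5 | −0.030 | −0.060 |
| 30% | half | 3.8 / 1.9 | −0.036 | −0.073 |
| 30% | all | 7.5 / 3.8 | −0.067 | −0.133 |
| 57% | half | 7.1 / 3.6 | −0.064 | −0.127 |
| 57% | all | 14.2 / 7.1 | −0.132 | −0.263 |

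Negative values run against the intervention. With risk ratio 1.0 and equal selection the shift is 0 in every case. Both arms then look too favourable, and the number analysed per arm falls to between 23.5 and 10.8.

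For comparison, the standard error of a difference between two arms of 25 is √(2/25) = 0.28 SD.

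**Step 3: the worst case.** Suppose removal is fully determined by the outcome, 30% of controls are removed and the true benefit is 0.5 SD. With lower scores better, controls N(0,1) cut at the 70th percentile have mean −0.497. The intervention arm N(−0.5,1) with the same cut loses 15.3% and has mean −0.779. The observed difference is 0.779 − 0.497 = 0.282 SD, a loss of (0.5 − 0.282)/0.5 = 44%.

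**The case against.** Five points can be made on the other side.

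**The wording may be narrower.** The parenthesis names only ambulatory assessment and intervention components, both of which end 8 weeks after discharge. Discontinuation could mean ending that active phase alone. This is possible but less literal, because what is discontinued is participation in the study. Even on this reading, collection of ambulatory outcome data stops early. The point stands as a need to say which is meant.

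**A large loss of effect is not shown.** A reader might infer that close to half the benefit disappears. The 44% needs removal to be fully determined by the outcome and 30% of controls to qualify. With 15% of controls removed and a correlation of 0.5, the same model gives 0.46 SD instead of 0.50, a loss of about 8%. This objection stands.

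**The model is not the planned test.** It compares scores at one time point, whereas the plan tests group by time. Whole-patient exclusion removes a patient's stable severity at every time point, and that part largely cancels in change over time. Only selection on worsening after discharge distorts the interaction. This stands too, and is a further reason to treat the table as scale only.

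**Readmission counts may be safe.** A reader might infer that repeat readmissions after a long stay are lost. The documents do not support this. Table 1 names hospital documentation as a source, and the section on hospital documentation adds controlling data. Neither needs survey participation, and the triggering stay can itself be recorded. The article simply does not say whether this collection continues.

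**An article condenses.** The absence of a stated analysis set or sensitivity analysis carries no weight here. The concern rests on two rules that are written down.

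**Conclusion.** The concern holds as a structural flaw of uncertain size. As written, an event closely tied to one primary outcome removes patients from the analysis of two others, and the complete-case rule discards their earlier data as well.

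The direction is conditional. If the aftercare does reduce long stays, the control arm loses more of its worst-course patients and the benefit on quality of life and symptoms is understated. If long stays are equally frequent and equally selective in both arms, the difference may be little affected, but the result then describes only patients without a long stay. If long stays were more frequent under the intervention, the sign would reverse. A flat statement that the comparison is biased would go beyond the documents, which give no arm-specific rates.

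The illustrative shift is about 0.02 to 0.26 SD against the intervention, on the assumed shares, risk ratio 0.5 and correlations 0.3 to 0.6. The upper end needs a 57% control readmission rate with every readmission qualifying. The case for changing the text does not depend on these numbers.

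**What to change.** 1. **Participants and recruitment.** Reword so that a long inpatient stay does not end assessment. The 8-, 24- and 36-week questionnaires and the readmission records continue to 36 weeks after index discharge for all randomised patients, who are analysed in their randomised group. When aftercare itself stops or resumes is left unchanged.
2. **Statistical analyses.** Replace whole-participant exclusion from the ANOVAs with a likelihood-based mixed model that uses all available time points. Both changes are needed. Without the second, one missed survey still deletes the patient; without the first, the model has no scores from after the long stay.
3. **While rewording.** The two branches cover stays of less than and more than 2 weeks. A stay of exactly 2 weeks falls under neither, and the sponsor should resolve this.

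The cost is a short amendment and a change of model. The surveys are already online and hospital documentation is already a data source. The downsides are a few extra survey contacts with families under strain and, since recruitment began in March 2021, only partial recovery of data for patients already discontinued.

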**Fig. 1 Fig1:**
[figure not shown]
Recruitment process

### Randomization and blinding

Participants are assigned to the intervention or control group after having given written informed consent to participate in the study. Children or adolescents, their parents, and their teachers are always assigned to the same group. A randomization list with equal proportions of both groups was generated with the software R (based on the function “sample”) [48] before the start of the study. Participants are successively assigned to one of the two groups according to the order of their recruitment (date of written informed consent) using the randomization list. Only after inclusion in the study, DigiPuR study staff look up the assignment in the randomization list and record the assignment in the coding list, which is kept locked in a cabinet and only accessible to the study management. They inform therapists about the group assignment by e-mail and participants during the technical briefing by a video or phone call or on site at the hospital. Blinding of participants, case-leading therapists, and conducting study staff is not possible due to the different nature of treatment in the two groups. Data evaluation, however, is blinded, as group allocation is coded without knowledge of the data analysts.

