#### Data security and storage

Procedure for data management was approved by the data protection officer and the IT security officer of the University Hospital Tuebingen, Germany. The collection and storage of all data is pseudonymized and stored for 10 years. All questionnaires are labeled with an anonymous personal code of the participant. Data can only be assigned to individuals based on a coding list, which is continually updated by hand, kept locked, and only accessible to study management. The coding list will be destroyed at the end of the study.

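### The randomization list is read by the staff group that also identifies participants, and nothing described shields its later entries, so concealment of upcoming assignments is not secured

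*Protocol article*

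**What the plan says.** The section Randomization and blinding sets out the procedure step by step:

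- The list was prepared in advance: "A randomization list with equal proportions of both groups was generated with the software R", using the function sample.
- Families take entries in sequence, "according to the order of their recruitment (date of written informed consent) using the randomization list".
- The look-up is done by study staff: "Only after inclusion in the study, DigiPuR study staff look up the assignment in the randomization list".
- Staff then "record the assignment in the coding list, which is kept locked in a cabinet and only accessible to the study management". They inform therapists by e-mail and participants at the technical briefing.
- Participants, therapists and the staff running the study are not blinded.

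Participants and recruitment gives the other half: "DigiPuR study staff are in weekly communication with the therapists in the department’s therapy wards and day hospitals to identify participants".

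Data security and storage again describes the coding list as locked and open only to study management, and presents it as the key that links data to persons. No section gives a holder, storage place or access rule for the randomization list.

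**The concern.** Concealment must hold for the next family as well as the current one. A person who opens a sequential list to read one line may see the lines that follow. If that person, or a close colleague, also helps decide whom to approach and when, the next assignment could influence the approach or the timing of consent, even without intent.

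Three features make this matter here.

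- **Wide discretion.** Exclusion criteria are deliberately minimal, and diagnosis, indication and time of discharge do not restrict entry.
- **Very different arms.** Under Interventions, control aftercare is the same as for patients who do not take part, usually one consultation at about 6 weeks. The intervention arm has six video calls and a messenger channel.
- **Small and open-label.** There are 25 children per arm. Of the four primary outcomes, satisfaction, quality of life and symptom severity are reported by people who know the assignment. Protection at allocation therefore carries more weight.

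The direction of any resulting bias is unknown. Steering children in greater need to the intervention would work against it, and steering children expected to do well would favour it.

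**Working it through.** No stated figure of the trial can be reproduced for this point. The check sets the described steps side by side, then asks how much foreknowledge each route could give.

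**Step 1. What each described safeguard covers**

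| Element | Where | What it protects |
|---|---|---|
| Consent and inclusion before look-up | Randomization and blinding | The assignment of the family being enrolled |
| Lock and restriction to study management | Randomization and blinding; Data security and storage | The coding list, which holds past assignments |
| Holder, storage or single release of the randomization list | Not described | – |

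The first safeguard works for family *i*. Once the list has been opened for family *i*, nothing described hides the entry for family *i* + 1 from staff still recruiting. The second safeguard concerns another document. Even if the randomization list shared the same cabinet, those doing the look-up would still handle it.

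**Step 2. Foreknowledge without sight of the list**

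Assume one unblocked sequence with exactly *n* = 25 entries per arm. The article gives equal proportions and 25 children per group, but no list length. Someone who knows all past assignments and always guesses the arm with more entries left is expected to be right

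*n* + ½ × (4ⁿ / C(2n, n) − 1) = 25 + ½ × (8.907 − 1) = 28.95 times of 50, or 57.9%.

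Chance alone gives 25 of 50. The expected number of final assignments that are fully determined is 2n / (n + 1) = 50 / 26 = 1.92.

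Past assignments therefore give little away.

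**Step 3. Foreknowledge with sight of the list**

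Every entry that is seen is known with certainty. The gap between 57.9% and certainty depends on whether the list is shielded, so custody is the issue.

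**Step 4. Possible bias, on assumed inputs only**

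The article gives no figure for steering. Suppose *k* children of one prognostic type are placed in one arm and *k* of another type in the other arm, where chance would have split both types evenly. If the types differ by *d* SD, the group difference shifts by (k / 25) × d.

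- *k* = 2, *d* = 0.5: 0.04 SD
- *k* = 5, *d* = 0.5: 0.10 SD
- *k* = 2, *d* = 1.0 (each type 0.5 SD from the average, in opposite directions): 0.08 SD
- *k* = 5, *d* = 1.0: 0.20 SD

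The standard error of a simple difference between two arms of 25 is √(2/25) = 0.28 SD, so these shifts are about 0.14 to 0.7 standard errors. The values of *k* and *d* are illustrative and are not evidence that steering occurred.

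**Step 5. Order of entries**

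The order is fixed by a date. Two families consenting on the same day have no stated order. This is a small gap that a time stamp closes.

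**The case against.** The strongest reply is that the article describes look-up only after inclusion, and nowhere says that staff see entries in advance. It is a condensed account: the recruitment figure is not reproduced here, the SPIRIT checklist is in a supplement, and either might describe a concealment step. Study staff is a group label. Because the assignment is recorded in a list open only to study management, those who look it up may be a subset who do not recruit. Under Interventions, study staff take no part in therapy.

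Much of this stands, and it limits what may be said.

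- A reader might infer that allocation is not concealed, or that all 50 assignments can be read in advance. The documents support neither, because they do not say how the list is stored or displayed.
- A reader might infer that therapists can steer patients. They are told each assignment only after look-up, and no access to the list is described for them.
- A reader might take the Discussion's remark, that enrollment is decided before assignment, as a claim about concealment. In context it concerns families weighing burden against benefit, and for that it is sound. It does not address selection by recruiters.
- It would be too strong to say that analysis can do nothing. Symptom severity and quality of life are measured at admission and discharge, and the test is group by time, so imbalance in those measures would be visible and partly handled. That does not extend to readmissions, or to satisfaction, which is measured only at 8 weeks.

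The reply does not remove the point. The article states a procedure, and that procedure places look-up and identification of candidates in the same named group. The objection is to that arrangement, not to a missing detail.

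**Conclusion.** The point holds in a limited form. As described, concealment of upcoming assignments rests on one rule, look-up after inclusion, and that rule does not cover the next family. Selective approach or timing of consent is possible. It is not shown to have happened, and the two tasks may be done by different individuals.

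The size cannot be derived from the document. Guessing from past assignments adds about 4 correct guesses in 50 over chance, if the list is one unblocked 25/25 sequence. Any material foreknowledge would have to come from sight of the list. The illustrative shifts of 0.04 to 0.20 SD rest wholly on assumed inputs.

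This is a cheap improvement that should be made. It does not show that the trial is biased.

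**What to change.** For the remaining recruitment:

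1. Have an existing department member with no role in recruitment or therapy hold the randomization list.
2. Release one assignment at a time, after consent has been logged with a time stamp that fixes the order.
3. State in the trial report who has had access to the list so far and how it was stored. If recruitment is already complete, this step alone remains.
4. Do not rely on consent before assignment alone as protection against selection by recruiters.

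The list need not be regenerated, and the models need no change. Permuted blocks would make guessing easier in this open-label trial: with a known block size of 4, the Step 2 formula with *n* = 2 gives 2.83 of 4 correct (70.8%), against 57.9% for the single list.

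The cost is at most 50 look-ups by a colleague, no new post, and a slight delay per patient. At the stated status date of 29 October 2021, about 8 of the 16 recruitment months (March 2021 to June 2022) remained, so the change was feasible then.
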